Seizure activity	Presence or absence of seizure activity on aEEG [45, 46].	Postnatal seizure activity and postoperative seizure activity	Proportion of neonates with seizure activity per group	Postnatal (until at least 24 h after birth) Postoperative (until at least 48 h after surgery)
Regional cerebral oxygen saturation	Regional cerebral oxygen saturation (%), lowest regional cerebral oxygen saturation (%), and duration of regional cerebral oxygen saturation < 45% (minutes) will be assessed by NIRS in intervals 0–3, 3–6, 6–12, 12–24, and 24–36 h after birth and 0–3, 3–6, 6–12, 12–24, 24–48, and 48–72 h after surgery [47, 48].	Postnatal regional cerebral oxygen saturation, postoperative regional cerebral oxygen saturation, and change between postnatal and postoperative regional cerebral oxygen saturation	Mean (and SD) or median (and IQR) per group	Postnatal (until at least 24 h after birth) Postoperative (until at least 48 h after surgery)
General movements	Assessment of general movements, using the motor optimality score [49–51].	Motor optimality score at 3 months	Mean (and SD) or median (and IQR) per group	3 months
Motor, cognitive, and speech/language development	Motor, cognitive, and language composite score of the Bayley-III-NL. An average Bayley-III-NL score is 100; one SD above or below the mean concerns 15 points [52].	Motor, cognitive, and language composite score at 24 months	Mean (and SD) or median (and IQR) per group and proportion per group below 1 SD	24 months
Quality of life	Parent-reported quality of life score using the TNO-AZL Preschool Children’s Health-Related Quality of Life questionnaire [53].	Parent-reported quality of life score at 24 months	Mean (and SD) or median (and IQR) per group	24 months
Cost-effectiveness of allopurinol	Questionnaires on the need for healthcare resources, productivity losses of parents, and expenses borne by families. Healthcare and societal costs will be determined with the Dutch guidelines for health economic evaluation.	Healthcare and societal costs at 3 months; healthcare and societal costs at 24 months	Mean (and SD) per group	3 months 24 months
Cost-effectiveness of allopurinol	Length of hospitalization and intensive care stay (days) and costs associated with hospitalization using standard unit prices from Dutch guidelines for health economic evaluation.	Healthcare costs	Mean (and SD) per group	24 months

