#### Neuromonitoring

Brain function will be assessed by amplitude-integrated electroencephalography (aEEG) and oxygenation by near-infrared spectroscopy (NIRS) at defined time points after birth (0–3, 3–6, 6–12, 12–24, 24–36 h) and surgery (0–3, 3–6, 6–12, 12–24, 24–48, 48–72 h) [45, 47]. Dominant background pattern and changes in background pattern over time (continuous normal voltage, discontinuous normal voltage, burst suppression, continuous low voltage, flat trace) and presence of sleep-wake cycling and seizure activity (absent, single seizure, repetitive seizures, status epilepticus, including response to anti-epileptic drugs) will be identified with aEEG [45]. The mean regional cerebral oxygen saturation (rScO_2_), lowest rScO_2_ (%), and duration of rScO_2_ < 45% will be assessed by NIRS [47]. Neuromonitoring will be performed after birth with continuation for at least 24 h, and after surgery with continuation for at least 48 h.

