#### Secondary analysis

Secondary analysis is based on the comparisons of secondary outcomes between the allopurinol and mannitol-placebo group, both for the total study population and separately for subgroups of CCHD. Additionally, a secondary analysis will be performed to assess an interaction with gender, as females possibly benefit more from allopurinol administration than males [30]. Descriptive statistics will be applied, including the independent sample *t*-test or the Mann-Whitney *U*-test for continuous data and Pearson’s chi-square test for categorical data. Safety analyses will be based on incidences of (serious) adverse events in both groups.

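### The last NIRS interval in each period (24–36 h after birth, 48–72 h after surgery) lies beyond the required monitoring, so its between-group comparison rests on infants who happened to stay on the monitor

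*Protocol article*

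**What the plan says.** Table 1 under Secondary outcomes has a row for regional cerebral oxygen saturation with three measures: the saturation itself, its lowest value, and "duration of regional cerebral oxygen saturation < 45% (minutes"). These "will be assessed by NIRS in intervals 0–3, 3–6, 6–12, 12–24, and 24–36 h after birth", and the list of intervals closes with "and 24–36 h after birth and 0–3, 3–6, 6–12, 12–24, 24–48, and 48–72 h after surgery". The time-point column of the same row reads "Postnatal (until at least 24 h after birth) Postoperative (until at least 48 h after surgery").

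The Neuromonitoring section repeats both elements. Assessment is "at defined time points after birth (0–3, 3–6, 6–12, 12–24, 24–36 h) and surgery (0–3, 3–6, 6–12, 12–24, 24–48, 48–72 h"), and a few lines later: "Neuromonitoring will be performed after birth with continuation for at least 24 h, and after surgery with continuation for at least 48 h".

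The Secondary outcomes section states that the listed outcomes are compared between the arms and that Table 1 gives all five elements of each outcome definition. The NIRS row is aggregated as "Mean (and SD) or median (and IQR) per group". The Secondary analysis section names the methods, "including the independent sample *t*-test or the Mann-Whitney *U*-test for continuous data", with no reference to monitored time. The missing-data section has one general sentence on multiple imputation. Nothing says which infants are monitored past the minimum, or why.

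**The concern.** A between-group comparison keeps the protection of randomisation only if each arm contributes all its infants, or loses them for reasons unrelated to treatment. The last interval in each period exists only for infants kept on the monitor longer than the plan requires, which is decided after randomisation. If allopurinol speeds recovery, fewer treated infants may still be monitored, and those who remain may be the sicker ones. The Background section makes this conceivable: it cites a study in tetralogy of Fallot repair in which allopurinol had beneficial effects on inotrope use, ventilation time and intensive care stay.

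A second, smaller problem sits in the same interval. Minutes below a threshold have no denominator, and a minimum can only fall or stay the same as recording continues. Both measures therefore vary with the part of the interval that was recorded. At stake is the reading of one secondary outcome. The primary endpoint, sample size and interim analysis are untouched.

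**Working it through.** The plan gives no figure on this point, so there is nothing to reproduce.

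**Step 1: intervals against required hours** (Table 1 and Neuromonitoring).

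| Period | Required minimum | Intervals inside it | Interval outside it | Share of window outside |
|---|---|---|---|---|
| After birth | 24 h | 0–3, 3–6, 6–12, 12–24 (4 of 5) | 24–36 h | (36 − 24)/36 = 12/36 = 33% |
| After surgery | 48 h | 0–3, 3–6, 6–12, 12–24, 24–48 (5 of 6) | 48–72 h | (72 − 48)/72 = 24/72 = 33% |

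In each period the part outside is exactly the whole last interval.

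**Step 2: exposure within an interval.** Expected minutes below 45% = p × recorded hours × 60, where p is the share of time below 45%. The documents give no p; 5% is assumed for illustration.

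- Required interval 12–24 h after birth: 0.05 × 12 × 60 = 36 min for every infant recorded throughout. Exposure is the same, so minutes are comparable.
- Last interval after birth: recorded to 36 h, 0.05 × 12 × 60 = 36 min; recorded to 30 h, 0.05 × 6 × 60 = 18 min; stopped at 24 h, no value.
- Last interval after surgery: recorded to 72 h, 0.05 × 24 × 60 = 72 min; recorded to 60 h, 0.05 × 12 × 60 = 36 min; stopped at 48 h, no value.

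The factor of 2 between a full and a half-recorded last interval holds for any constant p. As a percent of recorded time, all these infants score 5%.

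**Step 3: selection in the last interval.** This illustrates the mechanism; every input is assumed. Let mean saturation be 65 − 6s, with severity s standard normal and distributed alike in both arms, and no drug effect on saturation. Suppose only the sickest fraction c stays on the monitor. The observed mean is then 65 − 6 × φ(z)/c, where z is the normal quantile that cuts off the upper fraction c.

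- c = 50% in both arms: difference 0.
- c = 40% against 60%: φ(0.253) = 0.3863. The means are 65 − 6 × 0.966 = 59.20 and 65 − 6 × 0.644 = 61.14, a difference of 1.93 points.
- c = 30% against 70%: φ(0.524) = 0.3477. The means are 65 − 6 × 1.159 = 58.05 and 65 − 6 × 0.497 = 62.02, a difference of 3.97 points.

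The arm with fewer infants still monitored looks worse, because those who remain are more strongly selected. This is the extreme case, in which severity alone decides who stays on. If monitoring length is unrelated to severity, the difference is 0 whatever the fractions.

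**The case against.** **The text is not contradictory.** A minimum permits longer recording, and an extra interval for infants recorded longer is compatible with it. This stands. The fault is that the last interval is not guaranteed, and the plan nevertheless compares it between arms like the others.

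**The raw-minutes problem is easily overstated.** A reader might sum minutes over the whole window. At 5%, 24 h gives 72 min and 36 h gives 108 min; 48 h gives 144 min and 72 h gives 216 min, which is 50% more in each case. The documents do not support that reading: Table 1 assesses the measures per interval and states no sum over the window. In the required intervals a compliant infant has about full exposure, so only signal gaps, late starts or deaths can distort minutes or the lowest value. This stands and limits the point mainly to the last interval.

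**The selection mechanism is an inference.** No section says why monitoring continues past the minimum. Centre routine is an equally possible reason (Concomitant treatment), and randomisation is stratified by centre. Care providers are blinded, so the arms should differ systematically only through a real effect on the infant's course. This largely stands. Blinding does not remove that route, however, and the plan does nothing to exclude it.

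**Details of signal handling belong in the analysis plan.** For artefact rules and the definition of valid time, this is correct. The unit, intervals and time points are different: Table 1 fixes them. The general multiple-imputation sentence does not settle the matter, because hours that were never required to be recorded are not defined as missing.

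**The secondary analysis is already called descriptive.** True, but the same sentence prescribes t-tests or Mann-Whitney tests, with no distinction between guaranteed and non-guaranteed intervals.

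**Conclusion.** The point holds in limited form. The last NIRS interval in each period, 33% of each window, lies wholly outside the required monitoring. Its between-group comparison uses a subset formed after randomisation, and within it minutes below 45% and the lowest value also depend on the recorded part. The other four postnatal and five postoperative intervals are sound apart from signal gaps, late starts or deaths.

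The size of any bias cannot be derived from the documents, which give neither a desaturation rate nor the number monitored past the minimum. It is zero if continued monitoring is unrelated to treatment and clinical state. Under the extreme assumptions in the working it reaches about 2 to 4 saturation points. A reader might conclude that the NIRS results as a whole are biased, or that the arms will differ in monitoring time; the documents support neither. One secondary outcome is concerned, and the priority is minor.

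**What to change.** In Table 1 and the Neuromonitoring section:

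1. Confine the formal between-group NIRS comparison to 0–24 h after birth and 0–48 h after surgery.
2. Label the 24–36 h and 48–72 h intervals descriptive, and report the number of infants still monitored in each arm.
3. Replace minutes below 45% by percent of valid recorded time below 45%, per interval. Compare the lowest value only in the required intervals.

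This is a change of wording and derivation; no new data are needed beyond the recorded time per interval. The cost is that the last interval of each period leaves the formal comparison.

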### Intervention

Allopurinol 100 mg powder for infusion (PFI) or mannitol-placebo 100 mg PFI is reconstituted in 10 ml sterile water for injection (WFI). Each dose of 20 mg/kg, corresponding to a concentration of 2 ml/kg, will be delivered through peripheral or central line infusion over 10 min using a syringe pump. Blinding is secured as mannitol-placebo PFI has an identical appearance as allopurinol PFI, and with a dose of 20 mg/kg, no clinical effects are expected from mannitol-placebo PFI administration [38]. The study medication will be arranged in patient-dedicated boxes, containing 5 vials of PFI and WFI (prenatal group) or 3 vials of PFI and WFI (postnatal group).

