#### Prenatal group

In neonates that are diagnosed with CCHD before birth, allopurinol PFI or mannitol-placebo PFI 20 mg/kg body weight per administration will be administered early postnatally (within 45 (max. 60) min after birth and 12 h after the first dose), preoperatively (12 h prior to cardiac surgery), intraoperatively (at the start of CPB), and postoperatively (24 h after surgery) (Fig. 1).

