Cost-effectiveness of allopurinol	Motor, cognitive, and language composite score of the Bayley-III-NL [52] and healthcare and societal costs. Healthcare and societal costs will be determined with the Dutch guidelines for health economic evaluation.	Bayley-III-NL score, healthcare, and societal costs	Cost per point improvement in neurodevelopmental outcome per group	24 months
Pharmacokinetic evaluation of allopurinol	Allopurinol, oxypurinol, hypoxanthine, xanthine, and uric acid levels (mg/L) will be measured in blood samples collected around birth and surgery in 24 patients with a prenatal diagnosis [20, 32, 33, 54].	Allopurinol, oxypurinol, hypoxanthine, xanthine, and uric acid levels (mg/L)	Mean (and SD) or median (and IQR)	Postnatal (umbilical cord and 15–60 min, 4 h, 12 h, 13–14 h, 24 h, 36–48 h, and 96–168 h after birth) Perioperative (0–3 h before dose 3, 1–3 h after dose 3, 0–1 h before dose 4, at the end of CPB, 4 h after surgery, 0–3 h before dose 5, 1–3 h after dose 5, and 48 h after surgery)
Redox and antioxidant state of allopurinol	Enzyme-linked immunosorbent assay will be used to measure hypoxic tissue injury, overall redox and antioxidant state, lipid peroxidation, protein oxidation, and nitrosative state. Mass spectrometry will be used to determine allopurinol, oxypurinol, non-protein bound iron, and xanthine oxidase levels (mg/L) [12].	Hypoxic tissue injury, overall redox and antioxidant state, lipid peroxidation, protein oxidation, and nitrosative state Allopurinol, oxypurinol, non-protein bound iron, and xanthine oxidase levels (mg/L)	Mean (and SD) or median (and IQR) per group	Postnatal (umbilical cord) Perioperative (directly before surgery and 6 h, 1 day, 2 days, and 4 days after surgery)

*Abbreviations*: *aEEG* Amplitude-integrated electroencephalography, *Bayley-III-NL* Bayley Scales of Infant and Toddler Development - Third Edition - Dutch Norms, *BMI* body mass index, *CCHD* critical congenital heart disease, *CPB* cardiopulmonary bypass, *IQR* interquartile range, *MRI* magnetic resonance imaging, *NIRS* near-infrared spectroscopy, *SD* standard deviation

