#### Pharmacokinetics of allopurinol

In the first 24 neonates with a prenatal CCHD diagnosis in the UMC Utrecht, blood samples will be collected postnatally and perioperatively for pharmacokinetic evaluation of allopurinol. It is expected—depending on the randomization—that approximately 12 of these neonates received allopurinol PFI and 12 mannitol-placebo PFI. This analysis will be performed to extend knowledge on the current pharmacokinetic data of allopurinol, oxypurinol, hypoxanthine, xanthine, and uric acid and to establish if expected target concentrations of allopurinol > 2 mg/L are reached in CCHD neonates [54]. Blood sampling will be combined with clinically indicated samples and will be taken from pre-existent arterial or venous access lines.

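### The first pharmacokinetic sample after cord blood is timed from birth in a window that overlaps dose 1, so it is not guaranteed to be post-dose

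*Protocol article*

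**What the plan says.** Four parts of the protocol article bear on this point.

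- **Sampling after birth** (Secondary outcomes, Table 1, pharmacokinetic row): "Postnatal (umbilical cord and 15–60 min, 4 h, 12 h, 13–14 h, 24 h, 36–48 h, and 96–168 h after birth". Birth is the reference for the whole list.
- **Sampling around surgery** (same row): several samples are timed from a dose, for example "0–3 h before dose 3, 1–3 h after dose 3, 0–1 h before dose 4, at the end of CPB". The samples around dose 5 are also timed from the dose. Others are timed from the end of bypass or from surgery.
- **Dosing** (Intervention and Prenatal group): the two early doses are given "within 45 (max. 60) min after birth and 12 h after the first dose", and each dose is delivered "through peripheral or central line infusion over 10 min using a syringe pump".
- **Purpose and size** (Pharmacokinetics of allopurinol): the substudy covers the first 24 prenatally diagnosed neonates at one centre, of whom "approximately 12 of these neonates received allopurinol PFI and 12 mannitol-placebo PFI". One of its aims is to "establish if expected target concentrations of allopurinol > 2 mg/L are reached in CCHD neonates".

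Table 1 summarises the levels as mean and SD or median and IQR.

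**The concern.** The sampling window of 15–60 min and the period in which dose 1 may be given occupy nearly the same hour, and nothing in the row requires the sample to follow the dose. Two neonates sampled at the same nominal time could therefore contribute quite different quantities: one a baseline or mid-infusion level, the other a level after a completed 20 mg/kg dose.

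Two things are at stake. First, a mean or median by nominal time from birth would mix pre-dose and post-dose levels. Second, this is the only sample close to dose 1. The Discussion rests the case for early treatment on reaching target levels before hypoxic-ischemic events occur. If the sample comes too early, the 4 h sample is the next evidence on dose 1. With about 12 treated neonates, a few misplaced samples would matter.

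**Working it through.** The article states no figure for this point, so there is none to reproduce. The check compares the stated times.

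**Inputs from the article**

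- Dose 1 start: D min after birth, with limits of 45 and at most 60 min (Prenatal group).
- Infusion: 10 min (Intervention), so dose 1 ends at D + 10.
- First sample after cord blood: S, between 15 and 60 min after birth; next sample at 240 min (Table 1).
- Dose 2 starts 12 h after dose 1, at 720 + D, and ends at 730 + D.
- Samples near dose 2: at 720 min and at 780–840 min after birth (Table 1).

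**Assumptions, not in the article**

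- The 45 and 60 min limits apply to the start of the infusion, so it may end as late as 55 or 70 min.
- S is uniform over 15–60 min and independent of D.

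**Step 1. Share of samples drawn before dose 1 ends, for a fixed start**

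P(S < D + 10) = (D + 10 − 15)/45 = (D − 5)/45, limited to 0–1. The share drawn before dose 1 even starts is (D − 15)/45, limited in the same way.

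| Start of dose 1 (min) | Before the start | Before the end |
|---|---|---|
| 5 or earlier | 0% | 0% |
| 15 | 0/45 = 0% | 10/45 = 22% |
| 30 | 15/45 = 33% | 25/45 = 56% |
| 45 | 30/45 = 67% | 40/45 = 89% |
| 50 | 35/45 = 78% | 45/45 = 100% |
| 60 | 45/45 = 100% | 100% |

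**Step 2. The same share with starts spread evenly over a range**

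- 0–45 min: the share is zero up to D = 5, then rises linearly. The average is (40²/2)/(45 × 45) = 800/2025 = 40%.
- 15–45 min: the share is linear over the whole range, so take the midpoint: (30 − 5)/45 = 56%.
- 30–45 min: (37.5 − 5)/45 = 72%.

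If the 45 min limit applies to completion, starts run over 0–35 min. The share is then (30²/2)/(45 × 35) = 450/1575 = 29%.

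**Step 3. Gap to the next sample**

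240 − (D + 10) = 230 − D. This is 185 min for a start at 45 min and 170 min for a start at 60 min, or about 3 h.

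**Step 4. Dose 2**

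- The 12 h sample is at 720 min and dose 2 starts at 720 + D, so this sample is pre-dose.
- The 13–14 h window, relative to the end of dose 2, runs from 780 − (730 + D) = 50 − D to 840 − (730 + D) = 110 − D.
- For D = 45 it is 5 to 65 min after the infusion ends.
- For D = 60 it is −10 to 50 min, so 10 of 60 min (17%) fall during the infusion.
- Overlap requires D > 50.

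**Step 5. The same list read from dose 1**

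If time zero were the start of dose 1, 15–60 min would be 5–50 min after the infusion ends, 12 h would be the level just before dose 2, and 13–14 h would be 50–110 min after dose 2 ends. The list fits that reading well, so a slip in the reference point is possible. That is an inference; the table says birth.

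**The case against.** The strongest reply is that the limits are upper bounds and staff do not sample at random. A team that has just infused a study drug would probably draw its pharmacokinetic sample afterwards. The article is also condensed: the full protocol or a laboratory manual may require infusion and sampling clock times, and levels may be analysed by time since dose. The perioperative list mixes reference points as well, and other early measurements such as cerebral oxygenation are also timed from birth.

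Much of this stands, and it rules out stronger conclusions that a reader might draw:

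- **That the sample would usually precede the end of dose 1.** No actual times are given, and the share runs from 0% to 100% with the assumed start. The 89% figure needs every dose to start at the 45 min limit.
- **That peak exposure would be missed.** No peak parameter is named as an aim, and the table does not call this sample post-dose.
- **That the target question as a whole is lost.** The 4 h, 13–14 h and later samples also inform it, and dose 2 is largely covered.

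One part of the reply does not hold. Timing from birth is a stated rule in Table 1, not a detail left out of the article. Recorded clock times can relabel a sample drawn too early, but they cannot supply the early level after dose 1 that was never taken. For a start at 45 min, a sample after the infusion must fall between 55 and 60 min. For a start after 50 min, none can fall after it within the window.

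**Conclusion.** The point holds in a limited form. The stated sampling and dosing times overlap, so a compliant 15–60 min sample can be pre-dose, mid-infusion or post-dose. Under uniform sampling, the share drawn before dose 1 ends is 40% for starts spread evenly over 0–45 min, with the full 0–100% range possible. This rests on the assumed distributions and on the limits referring to the start of the infusion.

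The consequence is that the substudy may not show whether 2 mg/L is exceeded soon after dose 1, and that summaries by nominal time from birth would mix different quantities. It mainly concerns one time point in a secondary substudy of 24 neonates. Dose 2 is affected only if dose 1 starts later than about 50 min. The primary outcome, power and type I error are not involved.

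**What to change.** Reconcile the Prenatal group section with the pharmacokinetic row of Table 1:

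1. Time the first sample after cord blood from the end of dose 1 and, for consistency, the 13–14 h sample from the end of dose 2. The same row already times samples around doses 3 and 5 from the dose.
2. Summarise levels by actual time since dose. Apply this to samples already taken as well, since the first patient was enrolled in February 2020.
3. Judge whether the 2 mg/L target is reached after dose 1 only on samples drawn after that infusion ended, and report how many neonates have such a sample.

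Dosing, the number of samples and the blood volume do not change. The cost is a change of wording in the protocol and sampling instructions, and a small shift of some draws relative to the clinical samples with which they are combined. Samples already drawn too early can be relabelled but not replaced.
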